*Data collection*: Household survey data were previously collected by trained interviewers using an electronic tablet-based survey tool and uploaded to a password-protected server. Trained data clerks will collect routine cohort data from routine patient records and will input this data daily into a predesigned database. Clinical audit data will be collected on a paper-based checklist from routine patient records and entered into a purpose-designed Excel spreadsheet. Cost data will be obtained from accounting records, supply orders and staff observation. Qualitative data will be collected by trained interviewers using topic guides. The adherence survey will utilise adapted pre-existing self-report medication adherence and beliefs measures with data entered into a purpose-designed Excel spreadsheet.

*Data analysis:* Secondary analysis of the pre-existing household survey data will use descriptive methods and multivariate regression modelling. For the cohort study, descriptive analysis and multivariate logistic regression analysis will be used to explore the clinical outcome trends, complication rates, quality of care and guideline adherence that occurred during implementation of this model. Data from the clinical audit and from the adherence survey will be analysed using descriptive statistics. Costing analysis will describe total and unit costs and will compare cost levels and trends across different time periods as new programmatic elements were added. The qualitative research will use thematic analysis. Qualitative and quantitative data from the various data sources will be triangulated.

**Ethical considerations:** This study protocol will be submitted to the MSF Ethics Review Board and LSHTM Ethics Committee for ethics clearance. Written authorisation to implement the study will also be obtained from the MoH of Jordan.

**Dissemination:** Ongoing data from the study will be shared with local, national (including the Jordanian MoH) and international stakeholders every 6 months in order to inform and improve the delivery of NCD care by MSF and other public health agencies in the study area. Outputs will include reports and peer-reviewed academic publications and presentations at key conferences and workshops.

Table of Contents

Key data 2

List of acronyms 3

Executive Summary 4

1. Background 12

1.1 MSF Model of NCD Care in Irbid 13

1.1.1 NCD Service 14

1.1.2 Patient circuit 15

1.1.3 MSF NCD Clinical Guidelines 18

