1. Patients who have an NCD other than those named above are not admitted to the programme but are referred to the MoH or other service providers where available e.g. isolated hypothyroidism is referred to the International Rescue Committee clinic.

2. Co-morbid NCDs in addition to those named above, which may be treated at primary care level with medications included in the MSF Essential Drug List, are managed within the programme e.g. providing analgesia for osteoarthritis pain or anti-acid medications for gastritis.

3. NCDs that are not managed by the programme currently e.g. cancer, or complications of the named NCDs requiring secondary or tertiary care input, are referred to MoH services or to other NGOs where available e.g. retinal screening for diabetic patients is provided by the Qatari Red Crescent hospital in Irbid.

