| Implementation  To what extent was the intervention delivered as intended?  What are the facilitators and barriers to implementing the programme from a patient, provider and programmatic perspective?  What are the essential components and adaptations necessary to delivering an NCD service in this setting?  What are the start-up and incremental costs of delivering such a service? | Fidelity of programme delivery  (Process Indicators;  indicators in bold also reflect quality of medical care) | Extent to which clinical guideline delivered as intended:  Number / % of eligible patients with HTN with annual FPG performed during the reporting period  Number/ % of eligible patients with diabetes that have had an annual foot check/ eye check performed during the reporting period  Number / % of DM patients that have micro-albuminuria or urinary protein testing during the reporting period  Number / % of DM patients on ACE inhibitor (ACEi) with Creatinine testing during the reporting period  Number/ % asthmatics and COPD with control review (spirometry or clinical) during the reporting period  Number / % of active cohort attending a health education session at last clinical visit within reporting period  Number of MHPSS group sessions taking place monthly during reporting period  Number/ % of referred patients attending MHPSS individual counselling sessions  Number/ % of times when clinical action taken based on clinical or laboratory findings according to guideline (see Annexe 2d for detail) | Clinical audit  Participant observation  Routine health facility cohort data |
|  | Adaptations | NCD care adaptations to the local setting (e.g. cultural adaptations; dietary and exercise, smoking advice)  Programme adaptations related to humanitarian setting and role e.g. response to patients’ psychosocial needs and NCD-relevant mental health co-morbidities | Key informant interviews  Participant observation  Semi-structured interviews with 12 MSF/clinic staff and 16 patients |
|  | Cost | Staff time  Start-up and recurrent implementation costs (indirect, intermediate and final cost centres)  Average unit costs and unit costs stratified by morbidity) | Key informant interviews  2 Focus groups with  Medicine/supply/ staff costs  Staff time estimates |

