| “Effectiveness”/ Quality of Care  What are the trends in clinical outcomes and quality indicators of the programme?  What are the perceived benefits/unintended consequences from a patient and provider perspective? | Clinical Outcomes | No./% patients with hypertension that have a most recent BP <= 140/90 6 and 12 months post enrolment and trend from baseline  Number / % of patients with diabetes that have a most recent BP <= 140/90 6 and 12 months post enrolment and trend from baseline  Number / % of patients with diabetes with last HbA1c < 8.0 %/ 7.0 % 6 and 12 months post enrolment and trend from baseline  Number/% with a reduction of >= 0.5 mmol/L in cholesterol level from baseline 6 and 12 months from enrolment  Number/% of patients with asthma / COPD free from exacerbations/ admissions in the previous 6 months  Number / % of patients who report decreased/quitting smoking within reporting period  Number / % of patients who report increased levels of exercise from baseline during reporting period  Trend recommended referrals to another facility for acute complications/specialist care, as a proportion of active cohort | Routine facility cohort data  Costing data (for incremental costing analysis)  2 Focus group with patients  Semi-structured interviews with approximately 12 clinic staff and 16 patients |
|  | Quality Indicators | Proportion of recommended referrals to other services that are appropriate as per guideline  Number/ % of active patients with CVD prescribed a statin during reporting period  Number/ % of patients with CVD prescribed aspirin during reporting period  Number/ % of patients with CVD prescribed at least one anti-hypertensive during reporting period  Number/% of patients with COPD/asthma with inhaler technique check documented  Number/ % of times when appropriate clinical action taken based on clinical or laboratory findings according to guideline (see Annexe 2d for detail)  Trend in defaulters as a proportion of active cohort during reporting period  Description of cohort deaths (patient characteristics) | Clinical audit  Participant observation  Routine health facility cohort data |
|  | Perceived Effectiveness | Patient and providers perspectives on effectiveness of programme components (clinical review, medications, HE, HLO, MHPSS, HV) | Key informant interviews  2 Focus groups with patients  Semi-structured interviews with 12 MSF/clinic staff and 16 patients |

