Exacerbation of respiratory condition refers to self-reported or documented temporary, usually reversible, worsening of the condition requiring a step-up in treatment or hospitalisation, depending on severity. Acute referral to specialist care or to the emergency room is recommended by the NCD guideline when the condition is not controlled by the maximum available primary-level treatment; additional secondary-care level diagnostics or treatments are required; in an uncontrolled acute exacerbation; or in cases of clinical uncertainty. Specific referral criteria for each condition are further described in the guideline.

Other outcome measures are listed in Table 2 (page 26).

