## Annex 2e: Clinical audit sample checklist

|  | Condition | YES | NO | N/A |
| --- | --- | --- | --- | --- |
| 1.0 | Diabetes | | | |
| 1.1 | Micro-albuminuria or urinary protein tested in the last year (Target = 80%)  ? | Y | N | N/A |
| 1.2 | Correct action taken based on micro-albuminuria test result? (Target = 80%)  ? | Y | N | N/A |
| 1.3 | Baseline CVD risk score done on enrolment? | Y | N | N/A |
| 1.4 | Prescribed statin in accordance with guideline (if risk score > 20% or known CVD)? |  |  | N/A |
| 1.5 | On ACE inhibitor (ACEi) inhibitor for HTN if no contraindication (Target 80%)  ? | Y | N | N/A |
| 1.6 | Creatinine tested prior to ACEi initiation? (Target 80%) | Y | N | N/A |
| 1.7 | Annual foot check done? (Target 80%) | Y | N | N/A |
| 1.8 | Correct foot score calculated? (Target 80%) | Y | N | N/A |
| 1.9 | Correct action taken based on foot score? (Target 80%) | Y | N | N/A |
| 1.10 | Annual eye check done or referral made? (Target 80%) | Y | N | N/A |
| 2.0 | Hypertension | | | |
| 2.1 | Annual glucose check done if not known diabetic? (Target 80%) | Y | N | N/A |
| 2.2 | Correct action taken if above target (diagnose diabetes or perform second test as per guideline)? (Target 80%) | Y | N | N/A |
| 2.3 | Annual CVD risk score done? (Target 80%) | Y | N | N/A |
| 2.4 | Annual cholesterol checked if not prescribed a statin? (Target 80%) | Y | N | N/A |
| 3.0 | Asthma | | | |
| 3.1 | Annual control review done (Target = 80%) | Y | N | N/A |
| 3.2 | Action taken following control review as per guideline i.e. step down/up on medications as appropriate? (T 80%) | Y | N | N/A |
| 3.3 | Inhaler technique check documented? (Target 80%) | Y | N | N/A |
| 4.0 | Referral | | | |
| 4.1 | Referral to acute care/specialist service appropriate according to guideline? (T 80%) | Y | N | N/A |

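### For diabetes and CVD, the only non-fatal complication-type outcome pools acute with specialist referrals, so it cannot be read as a complication rate

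*Protocol*

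**What the plan says.** Table 2, Effectiveness/Quality of Care, Clinical Outcomes, contains one line on referrals: "Trend recommended referrals to another facility for acute complications/specialist care, as a proportion of active cohort". It does not separate the two kinds of referral and gives no favourable direction.

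The Executive Summary (Methods, data analysis) states that the cohort analysis will explore, besides clinical outcome trends, "complication rates, quality of care and guideline adherence that occurred during implementation of this model".

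On what is sent out of the programme, section 1.1.1 item 3 says that "complications of the named NCDs requiring secondary or tertiary care input, are referred to MoH services or to other NGOs where available", and the example it gives is that "retinal screening for diabetic patients is provided by the Qatari Red Crescent hospital in Irbid". Section 3.4.2 lists among the grounds for acute or specialist referral that "additional secondary-care level diagnostics or treatments are required".

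Table 2 also has a fidelity indicator for diabetic patients with an "annual foot check/ eye check performed during the reporting period". Annex 2e item 1.10 treats a completed annual eye check or an eye referral as success, with an 80% target. Section 1.1.6 says recommended specialist referrals are recorded at each visit and describes no field separating acute from planned ones.

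**The concern.** A clinical outcome needs a known good direction. Referrals for acute complications should fall if care limits complications, which section 2 gives as a focus of the model. Planned specialist and screening referrals should rise, at least at first, if the guideline is followed more closely. Section 1.1.4 lists introduction of the guideline among the changes made over time. A single trend that adds the two can go up, down or stay flat for reasons that have nothing to do with complications.

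At stake is what the report can say about diabetic and cardiovascular complications. Section 6 states that endpoints such as fatal and non-fatal myocardial infarction cannot be measured. Beyond this line, Table 2 and section 3.4.2 offer disease-control measures (blood pressure, HbA1c, cholesterol) and process measures for these two disease groups, but no other non-fatal complication measure.

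**Working it through.** **1. Can planned referrals enter the indicator?** The protocol does not say that they do or that they do not. Four places bear on it:

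- Table 2 names specialist care next to acute complications, without restricting it to unplanned care.
- Section 1.1.1 item 3 illustrates referral to outside services with retinal screening.
- Section 3.4.2 includes secondary-level diagnostics and clinical uncertainty among the referral grounds.
- Section 1.1.6 describes no field that would let an analyst drop planned referrals.

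A plain count of recommended referrals would therefore include eye-screening referrals wherever they are recorded as specialist referrals.

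**2. Does another indicator separate them?** The proportion of referrals that are appropriate (Table 2 and section 3.4.2) does not, because an appropriate referral can be of either kind. Audit item 4.1 also pools acute care with specialist services. The comparison of entry periods in section 3.4.5 compares the same pooled quantity between groups.

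**3. Illustration.** The protocol gives no figure to reproduce. Apart from the 80% target, every input below is an assumption. Let a = acute referrals per active patient, d = diabetic share of the active cohort, c = annual eye-check coverage, and f = the fraction of that coverage reached through a referral counted in the indicator, with one such referral per diabetic patient.

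Pooled indicator = a + d × c × f

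It rises when d × f × (gain in c) is greater than the fall in a.

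Take first f = 1, the case most favourable to the concern. The grid is d = 20, 40, 60%; c rising from 20, 40 or 60% to 80%; and a unchanged at 5%, or halved from 10% to 5% or from 20% to 10%. That gives 3 × 3 × 3 = 27 scenarios. The pooled indicator rises in 23 and falls in 4. It rises in all 9 with unchanged a, and in 14 of the 18 in which a is halved.

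| d | c | a | Pooled before | Pooled after |
|---|---|---|---|---|
| 40% | 40% to 80% | 5% to 5% | 0.05 + 0.40 × 0.40 = 21% | 0.05 + 0.40 × 0.80 = 37% |
| 40% | 40% to 80% | 10% to 5% | 0.10 + 0.40 × 0.40 = 26% | 0.05 + 0.40 × 0.80 = 37% |
| 20% | 60% to 80% | 20% to 10% | 0.20 + 0.20 × 0.60 = 32% | 0.10 + 0.20 × 0.80 = 26% |

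In the second row acute referrals halve and the indicator goes up. In the third it goes down, but by 6 points where acute referrals fell by 10.

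**4. Dependence on f.** Item 1.10 is met by a check or a referral, so 80% is not a referral rate and f may be well below 1. For the second row the change is −0.05 + 0.40 × 0.40 × f = −0.05 + 0.16f. This is zero at f = 0.05/0.16 = 0.31. Below that the pooled indicator falls. At f = 0 it goes from 10% to 5% and screening causes no distortion.

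**The case against.** The strongest reply is that screening may not be counted at all. The grounds in section 3.4.2 are introduced as those for acute referral, and routine screening of a stable patient is not among them. Annex 2e keeps the eye check (item 1.10, under Diabetes) apart from referral to acute or specialist services (item 4.1). This stands as far as it goes: the documents leave the question open, so the defect is a definition that permits mixing, not proof that mixing occurs. A reader might infer that the trend must rise as screening improves. That does not follow, since it needs the screening referrals to be counted and to outweigh any fall in acute ones.

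A reader might also infer that the protocol has no other complication outcome. It has: freedom from asthma/COPD exacerbations or admissions is a principal clinical outcome, and deaths are described. The gap concerns non-fatal complications of diabetes and CVD.

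The indicator is also minor. It is not among the principal outcomes of section 3.4.2, it is worded as a trend in referrals, and the protocol disclaims formal evaluation of effectiveness. The intention to explore complication rates appears in the Executive Summary and is not repeated in section 3.4.5. All of this limits the weight of the point. It does not give the line a direction, nor supply another measure for what the summary announces.

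Finally, coding referrals by reason could be left to an analysis plan that is not shown. But the pooling is in the stated outcome itself, which an analysis plan would be expected to follow.

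**Conclusion.** The point holds in a limited form. For diabetes and CVD, the one non-fatal complication-type outcome in Table 2 combines referrals that should fall with referrals that good care may increase. As written it has no clear reading and cannot supply the complication rates named in the Executive Summary.

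The size cannot be derived from the protocol. The grid shows only that the direction can reverse under plausible-looking inputs. It rests on assumed diabetic shares, acute referral rates and starting coverage, and on all eye coverage being reached by counted referrals. No particular multiple should be quoted; one obtained by treating the 80% target as a referral rate would misread item 1.10. The consequence is confined to one descriptive, non-principal indicator and to what is concluded from it about complications.

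**What to change.** Replace the single line in Table 2 with two:

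- (a) Under Clinical Outcomes: recommended referrals for acute complications or emergency care, per active patient, with a fall read as favourable.
- (b) Under the quality or fidelity indicators: planned specialist and screening referrals, with the reading direction stated. The annual eye check is already a fidelity indicator, so say how (b) relates to it.

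Base any statement on complications on (a) only, and align the Executive Summary wording with it. Report referrals with no recorded reason as a separate unclassified group.

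The cost is a wording change and one classification variable applied to referrals already recorded at each visit. Where the database does not hold the reason, the paper file must be checked or the referral left unclassified; a large unclassified group would weaken (a), so its size should be shown by period. No change to clinical practice is involved.

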### 1.1.1 NCD Service

The MSF NCD programme’s target population comprises urban-based Syrian refugees, both United Nations High Commissioner for Human Rights (UNHCR) registered and unregistered, and vulnerable Jordanians (those not entitled to or otherwise unable to access subsidised Ministry of Health services). At present, MSF is the only provider of free primary-level, specialised NCD care to Syrian refugees in Irbid governorate; other non-governmental organisations (NGOs) require co-payments for similar services. In December 2014, MSF commenced an NCD programme in Irbid within an MoH primary care centre at Ibn-Sena. A second clinic was opened at Ibn-Rushd in April 2015 alongside a private medical organisation. In 2016, a separate, similar NCD programme was opened by MSF-Operational Centre Barcelona (MSF-OCBA) in Ramtha, a border town in Irbid governorate, but it is not included in this cohort evaluation.

To date (November 2016), over 3500 patients have been enrolled in the Irbid programme. The service initially consisted of triage by nurses, routine medical review by doctors, health education provided by health promoters at each clinical contact, and provision of free medications dispensed from the on-site pharmacy by trained pharmacists. Specific programme components were added over time in response to emerging patient, programmatic and contextual needs: a mental health and psychosocial support (MHPSS) service for patients with specific indications; a humanitarian liaison officer who links patients to other humanitarian services; and a home visit service for frail or immobile patients.

The MSF NCD programme focuses on the four most common NCDs or NCD risk factors, which were responsible for the highest mortality amongst Syrians before the current conflict^2^: cardiovascular disease (CVD), including: hypertension (HTN), myocardial infarction, angina pectoris, stroke, transient ischaemic disease, peripheral vascular disease; diabetes mellitus types I and II (DM); asthma and chronic obstructive pulmonary disease (COPD); and co-morbid mental health issues which may impact on NCD care, such as bereavement, anxiety and depression. Patients with these named NCDs or risk factors are admitted to the programme and the programme guidelines, treatment protocols and data collection tools focus on these diseases. Other NCDs are managed in different ways as follows:

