**Table 1. Standard epidemiological and quality indicators for MSF NCD services**

### 1.1.4 Evolution of model of care

| **Epidemiological / service activity indicators** | **Quality indicators** |
| --- | --- |
| Number / % of new patient consultations per month | Number / % of DM patients that have micro-albuminuria or urinary protein testing in the last year (Target = 80%) |
| Number / % of follow-up consultations per month (% of total visits) (by age, gender, nationality) | Number / % of patients with DM or on ACE inhibitor (ACEi) with Creatinine testing in last year (Target 80%) |
| Number/ % of patients presenting with the following morbidities: DM Type I, DM Type II, Hypertension,  other CVD, Asthma, COPD, Hypothyroidism, other | Number/ % asthma and COPD patients who receive control review (spirometry or clinical) in last year (Target = 80%) |
| Number of new diagnoses over a period of time | Number/% of asthmatics with acute exacerbations/ admissions in last year (Target = 20%) |
| Number/ % of exits per month: % defaulter, % dead (by primary diagnosis),  % self-transferred, % other | Number / % of DM patients/ hypertensives with mean BP <= 140/90 over last 12 months  (Target = 80%) |
|  | Number / % of DM patients with mean HbA1C < 8.0 % (or average FPG<150) in last 12  months (Target = 80%) |

Programmatic changes over time include introduction of: (1) a home visit team (2) a humanitarian liaison officer and (3) a formal MHPSS service. Technical changes introduced over time include: (1) task shifting to nurses of follow-up consultations (2) introduction of MSF-OCA NCD Guidelines and (3) implementation of spirometry. Contextual changes that occurred since programme inception include: (1) introduction of co- payments by the Jordanian government for Syrian refugees accessing MoH primary care services in November 2014 (2) increased recruitment of vulnerable Jordanians to the MSF NCD programme in the last quarter of 2015 and (3) closure of the MSF NCD programme to new patients from May to October 2016.

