### 3.4.2 Cohort study main outcome measures

The principal **clinical outcome measures** for patients in the cohort are:

DM: HbA1c < 7 or 8%; proportion of patients meeting individualised target at last visit within the reporting period and trend from baseline

Hypertension: BP < 140/90 mmHg: proportion of patients at target at last visit within the reporting period and trend from baseline

Cardiovascular disease: change in total cholesterol level from baseline

Asthma / COPD: Free from exacerbations / admissions in last six months

The principal **quality of care outcome measures** are the following:

Number/ % of active patients with CVD prescribed a statin during reporting period

Number/ % of patients with CVD prescribed aspirin during reporting period

Number/ % of patients with CVD prescribed at least one anti-hypertensive during reporting period

Number/% of patients with COPD/asthma with inhaler technique check documented

Number/ % of times when appropriate clinical action taken based on clinical or laboratory findings according to guideline (see Annexe 2e for detail)

Description of trends and patient characteristics in programme defaulters and deaths

Proportion of recommended referrals to other services that are appropriate as per guideline

Death is defined as confirmed death reported by family or community member. A defaulter is defined as a patient who has not attended any NCD clinic appointments within the last 90 days, is not known to have died or moved out of the area, and has not been successfully contacted by phone on two occasions by the clinic registrar. The definition was changed in October 2016 to reflect the newly extended appointment interval for stable patients to: two consecutive missed appointments; not known to have died, moved out of the area, or become immobile and ineligible for home care; and has not been successfully contacted by phone on two occasions by the clinic registrar.

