### 3.4.3 Cohort data sources

The cohort will use retrospective routine facility data collected from files of patients admitted from the start of January 2015 to the end of December 2016. Data on costs for the economic analysis will be obtained from logistics supply, accounting and pharmacy records, and from time estimates obtained through observation and discussions with staff (see below for more details).

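### Dividing defaulters by the current active cohort turns a constant default risk into a rising trend, because recent entrants cannot yet be defaulters

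*Protocol*

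**What the plan says.** Among the quality indicators in Table 2, the protocol lists "Trend in defaulters as a proportion of active cohort during reporting period". Section 3.4.2 places default among the principal quality of care measures: "Description of trends and patient characteristics in programme defaulters and deaths".

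The same section gives the definition: "A defaulter is defined as a patient who has not attended any NCD clinic appointments within the last 90 days". The patient must also not be known to have died or moved away, and two phone contacts must have failed. It then adds: "The definition was changed in October 2016 to reflect the newly extended appointment interval for stable patients to: two consecutive missed appointments".

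The cohort draws on "files of patients admitted from the start of January 2015 to the end of December 2016" (section 3.4.3). Three dates govern its growth:

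- "In December 2014, MSF commenced an NCD programme in Irbid within an MoH primary care centre at Ibn-Sena" (section 1.1.1)
- "A second clinic was opened at Ibn-Rushd in April 2015 alongside a private medical organisation" (section 1.1.1)
- "closure of the MSF NCD programme to new patients from May to October 2016" (section 1.1.4)

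The protocol does not define the active cohort, and it does not restrict it to patients enrolled long enough to default.

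**The concern.** The numerator and denominator refer to different groups. Patients declared defaulters in a quarter stopped attending at least 90 days earlier, so they come from the cohort as it stood about three months before. The denominator is the cohort now, including everyone who joined in between.

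In a programme of stable size this would matter little. Here the cohort starts from nothing in January 2015, grows, and then has six months without entrants. The share of patients who cannot yet be defaulters moves from all of the cohort to none of it, for reasons unrelated to retention. The ratio is to be read as a trend, so a team could report worsening default when the risk had not changed, or could miss a real improvement hidden by the artefact. The distortion arises before the October 2016 change of definition and does not depend on it.

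**Working it through.** The protocol states no figure for this indicator, so there is none to reproduce. The check asks what the ratio shows when the true risk is constant.

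**Inputs from the protocol:** a window of January 2015 to December 2016 (eight quarters), a 90-day lag, and no intake from May to October 2016.

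**Assumptions:** a constant probability h = 2% per month of stopping attendance (1% and 3% also tried), flat enrolment in open months, the 90-day rule throughout, and an active cohort consisting of everyone enrolled and not yet declared. Cohort size cancels out of the ratio.

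**True value:** 1 − (1 − 0.02)³ = 5.88% per quarter.

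**Quarter 2 by hand.** Let n patients enrol per month.

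- Those declared in quarter 2 stopped in quarter 1. The 3n entrants of quarter 1 were in care for 1.5 months on average, giving about 3n × 1.5 × 0.02 = 0.09n.
- The active cohort goes from 3n at the start of quarter 2 to 6n − 0.09n = 5.91n at the end, with a mean of about 4.5n.
- Start-of-quarter denominator: 0.09/3 = 3.0%. Mean: 0.09/4.5 = 2.0%. Quarter-end: 0.09/5.91 = 1.5%.

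**All quarters, daily model.** With daily risk d = 1 − (1 − h)^(12/365.25) and entrants e on day t: stopping s(t) = A(t−1)·d; attending A(t) = A(t−1) − s(t) + e(t); declared D(t) = s(t−90); active C(t) = C(t−1) + e(t) − D(t). The ratio is the quarter's sum of D over C.

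| Quarter | 1 | 2 | 3 | 4 | 5 | 6 | 7 | 8 |
|---|---|---|---|---|---|---|---|---|
| Mean cohort, % | 0 | 2.0 | 3.6 | 4.3 | 4.6 | 5.1 | 6.0 | 5.8 |
| Quarter-end cohort, % | 0 | 1.5 | 3.0 | 3.8 | 4.2 | 5.1 | 6.2 | 5.4 |
| Start-of-quarter cohort, % | – | 3.0 | 4.5 | 4.9 | 5.1 | 5.2 | 5.9 | 5.9 |
| Enrolled under 90 days at quarter end, % of cohort | 100 | 51 | 34 | 26 | 22 | 7 | 0 | 14 |
| True risk, % | 5.9 | 5.9 | 5.9 | 5.9 | 5.9 | 5.9 | 5.9 | 5.9 |

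**Contribution of the closure.** Without it, quarter 7 would be 5.0% (mean), 4.7% (quarter-end) or 5.4% (start of quarter). The closure therefore adds 1.0, 1.5 or 0.5 points. The rest of the rise is start-up lag.

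**Sensitivity, mean cohort, quarter 2 to quarter 7:**

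- h = 1%: 1.0% to 3.0% (true 2.97%). h = 3%: 3.0% to about 9% (true 8.73%).
- Enrolment doubled from April 2015: 1.5% to 6.0%.
- Lag of 60 days: 3.3% to 6.1%. Lag of 120 days: 0.9% to 5.8%.

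A coarser monthly model at 2% gives between 1.0% and 3.9% in quarter 2, depending on whether entrants are at risk in their first month and on the denominator. Every version rises.

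**Check of the remedy.** Default declared by six months after entry requires last attendance within the first three months. At h = 2% this is 5.88% for every entry quarter (2.97% at 1%, 8.73% at 3%), so a constant risk gives a flat series.

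**The case against.** The strongest reply is that the protocol leaves the details open. Neither the active cohort nor the reporting period is defined, Table 2 is a summary, and an analysis plan could choose a denominator that removes the problem. Section 3.4.5 compares patients by period of entry, and Table 2 (Maintenance) counts those still active six months after enrolment, which is largely immune. Sections 2, 3.4 and 6 disclaim formal evaluation of effectiveness.

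Part of this stands. A narrower definition would remove the artefact, and its size depends on the denominator: with the start-of-quarter cohort, the quarter 2 shortfall is about half (3.0% against 5.9%) rather than about three quarters (1.5% against 5.9%). But the protocol does state a ratio and calls for its trend, and the natural meaning of its words includes new patients. The entry-period comparison is general and is not tied to this indicator, and the six-month measure is separate. Because the evaluation is descriptive, the trends are themselves the evidence.

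Three stronger readings are tempting but not supported:

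- A reader might infer that the 2016 closure drives the rise. It contributes 0.5 to 1.5 points in quarter 7, and the ratio with the mean or quarter-end cohort dips after intake reopens.
- A reader might infer that the trend will be used to judge the home visit service (August 2015) or mental health support (April 2016). No section says so.
- A reader might infer that any single percentage shortfall is a property of the plan. Each depends on an assumed risk, an assumed pace and one choice of denominator.

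**Conclusion.** The point holds. Read plainly, the indicator in Table 2 shows a rise in default under a constant risk. At 2% per month and flat enrolment, the quarterly ratio goes from about 1–3% in quarter 2 to about 6% in quarter 7, while the true figure stays at 5.9%. The direction held for every risk, enrolment pace, lag and denominator tried. The size is illustrative, because the protocol reports neither a default rate nor monthly enrolment. The conclusion rests on the active cohort including recent entrants, which the document implies but does not state. It affects one principal quality measure and should be corrected before the trend is interpreted.

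**What to change.** Replace the ratio with a measure aligned to time at risk, in one of two forms:

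- cumulative default, or Kaplan-Meier retention, at fixed times such as 6 and 12 months since cohort entry, shown by entry period. This fits the six-month indicator in Table 2 and the entry-period comparison in section 3.4.5; or
- defaults dated at the last attended visit, per 100 person-months, by calendar quarter.

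In either form:

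- Start risk time at the second visit. Section 3.4.1 admits only patients with two or more recorded visits, so earlier time is free of default by construction.
- Apply one default definition across the whole window where visit dates allow, and say so where they do not. Appointment intervals were lengthened in 2016, so a 90-day rule may not mean the same thing before and after.
- End follow-up early enough before the end of the records for the chosen definition to be met.

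If the programme ratio is still shown, define the active cohort, limit the denominator to patients enrolled long enough to meet the definition, and do not interpret the unadjusted ratio as a trend in default.

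The cost is a change of analysis wording. Section 1.1.6 describes visit-level records entered daily, so no new data collection is needed. The downside is that the last months of the window yield no default estimate. If records end in December 2016, patients entering after June 2016 cannot contribute complete six-month follow-up.
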